### Assessment and outcome measures

Assessment is aimed at investigating the clinical and functional status of the patients and evaluating the main effects of treatment on the primary and secondary outcome measures (Table 3). The primary outcome is the patient’s adherence to pharmacotherapy, intended as the continuous use of the primary prescribed drug. Even if patients with psychosis are generally under poly-pharmacotherapy, only adherence to the most important drug (the one expected to produce the main therapeutic effect), as indicated by the enrolling unit, will be monitored during the study. Adherence will be checked by a triple method of assessment: patient’s self-report on the Medication Adherence Rating Scale (MARS), patient’s replies to the four-query interview of the Brief Adherence Rating Scale (BARS), and measurement of blood levels of the prescribed drug. Data will be analyzed using two indicators of adherence:

1. a dichotomic index, where non-adherence is the lack of adherence to the treatment in 30% or more of the monthly evaluation on the self-report or the interview (since replies on both measures might not coincide);

2. a continuous index based on the scale - self-report or interview - which could be the most reliable by comparison with the measurement of blood levels of the primary prescribed drug, to apply statistical analyses of covariance and verify the impact of confounding variables on the primary outcome.

**Table 3 T3:** Timing of assessments of endpoints for efficacy and safety

	**T0**	**T1**	**T2**	**T3**
Background information (age, sex, diagnosis, and so on)	X			
Clinical Global Impressions	X	X	X	X
Brief Psychiatric Rating Scale (BPRS)	X	X	X	X
Positive And Negative Syndrome Scale (PANSS)	X	X	X	X
Social Performance Scale	X	X	X	X
Health of the Nation Outcome Scales (HoNOS)	X	X	X	X
World Health Organization Quality Of Life (WHOQoL)	X	X	X	X
The Family Questionnaire	X	X	X	X
Medication Adherence Rating Scale	X	X	X	X
Brief Adherence Rating Scale	X	X	X	X
Dosage Record and Treatment Emergent Symptoms Scale (DOTES)	X	X	X	X
Sheenan-Suicidality Tracking Scale (S-STS)	X	X	X	X
Modified Overt Aggression Scale (MOAS) 1.0	X	X	X	X
Blood sample for assessing of the blood level of the prescribed drug	X	X	X	X
Assessment of blinding				X

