A number of related, secondary outcomes will be assessed: the occurrence of psychotic symptoms, according to the Brief Psychiatric Rating Scale (BPRS) and the Positive and Negative Syndrome Scale (PANSS); the general level of psychopathology, according to the Health of the Nation Outcome Scales (HoNOS); changes in social functioning, according to the Personal and Social Performance scale (PSP), and in the quality of life, as evaluated on the WHO-Quality of Life-Short form (WHOQOL-Bref); changes in the patient’s overall clinical status, as measured by the Clinical Global Impression (CGI); changes in the dosage of the prescribed drugs, as a reflection of changes in adherence to therapy; and, finally, changes in the frequency of relapse and readmission. Italian validated versions of the scales will be used. The BARS and the Family Questionnaire (see below) were translated for this study.

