### Assessment tools

The MARS is a ten-item yes/no self-report instrument. Total scores vary from 0 (low likelihood of medication adherence) to 10 (high likelihood). From this scale, we used the five items specifically referring to the taking or not of the medication [31,32]. Therefore in our MARS version, total scores vary from 0 (low likelihood of medication adherence) to 5 (high likelihood).

The BARS is a brief, pencil-paper, clinician-administered adherence assessment instrument [33]. The BARS consists of four items: three questions and an overall visual analog rating scale to assess the percentage of doses taken by the patient in the past month (0% to 100%). The visual analog scale rating serves as a final adherence determination. The three questions inquire about patients’ knowledge of their own medication regimen and episodes of missed medication taking, and include: number of prescribed doses per day (question 1); number of days, over the past month, the patient did not take the prescribed doses (question 2); and number of days, over the past month, the patient took less than the prescribed doses (question 3). A higher score on the BARS corresponds to better adherence.

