### Medication

The study is open about the psychopharmacological treatment, with no treatment restrictions. On the basis of the study’s sample size, we expect equal distribution of type (classical versus atypical antipsychotics), dose, rate of non-adherence to medication, and prescription of other psychopharmacological treatment (antidepressants, mood stabilizers, benzodiazepines) in both treatment groups. Since the type and medication dose are potential confounders, they will be controlled.

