### Data management and analysis

All analyses will be based, as far as possible, on the intention-to-treat principle. Differences in the primary outcome (adherence to pharmacotherapy) will be analyzed with a two-tail test for proportions with the Miettinen exact test [61]. A multiple logistic regression will be carried out to control for the confounding variables [62] using adherence (yes/no) as the outcome to verify the impact of the FPP on controlling the impact of the confounding variables (sex, age, severity of the disorder, cluster).

Survival analyses will be performed using the Kaplan-Meier method, followed by the log-rank test to define the terminal events at both the start of non-adherence and the first relapse or readmission episode [63]. Intention-to-treat will be applied considering the primary and secondary outcomes [64]. Multiple imputations will be applied to integrate missing data [65].

As far as validation of the self-report (MARS) and the interview (BARS) measure of adherence with respect to the blood levels of the main prescribed drug is concerned, Spearman’s rho will be used to compare blood levels of the main drug with the self-report or the interview; partial correlation will be used to ascertain the links between blood levels of the main drug with the self-report or the interview by taking into account the other measures (the interview or the self-report, respectively).

All analyses will be done with Excel (Microsoft Excel 2013 running on Windows 8) (Chicago, IL 60606, USA) or the Statistical Package for Social Science (SPSS) version 17 for Windows.

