### Ethical considerations

The FPP is not expected to produce relevant somatic side effects but it can produce unwanted or unforeseen effects, such as an increase in the intra-family level of conflict. To maximize safety for the patients, before randomization each patient will be evaluated on his or her risk of unwanted or unforeseen effects attributable to exposure to the FPP.

The therapists involved in the administration of the FPP and GT will be monitored to minimize any improper method of administration of the protocol of treatment; assessors will also be trained and monitored to avoid dispersion of information, thus violating the guaranteed criterion of good faith in case of patients’ disclosing sensitive information. Data recording and storage will comply with the privacy law in force, and informed consent for information recording will be obtained from each patient.

Participation in the study is voluntary and written informed consent is obtained. Before enrollment, participants will receive both verbal and written assurance that they can withdraw from the trial any time, with no consequence for their continued treatment. Patients unable to give informed consent in an appropriate way or who refuse to participate in the study will not be enrolled.

The Training Center is committed to monitoring the quality of assessment and of the administration of the FPP procedures, on a three-month basis.

A paradoxical, unintended effect of greater adherence to pharmacotherapy is the potential increase of the somatic side effects of the prescribed drugs. Indeed, there is some indirect evidence that this can actually occur [66]. To limit this paradoxical effect, patients will be closely monitored for side effects and somatic conditions on a three-month basis or as needed. It is expected that, following improvement in the response to the therapy as a result of greater adherence to pharmacotherapy, the therapist will decrease dosage of the prescribed drugs. This specific change will be checked at assessment and a reduction of dosage of the prescribed drugs and of poly-pharmacotherapy is among the secondary outcomes of the study.

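### The validation of MARS and BARS against blood levels has no term for prescribed dose or drug, so its correlations are attenuated (minor, cheap to mend)

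*Protocol article*

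**What the plan says.** The Aims section calls blood levels the objective gold standard against which the self-report (MARS) and the interview (BARS) will be validated. Under Assessment and outcome measures, the continuous adherence index is to be based on whichever scale "which could be the most reliable by comparison with the measurement of blood levels of the primary prescribed drug".

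Data management and analysis gives the method. Spearman's "rho will be used to compare blood levels of the main drug with the self-report or the interview", and a partial correlation then relates level to one scale "by taking into account the other measures (the interview or the self-report, respectively". No other conditioning variable is named.

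Four other places bear on dose:

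- Medication: drug treatment is open and unrestricted. After a sentence expecting balance between the arms, the section adds: "Since the type and medication dose are potential confounders, they will be controlled".
- Assessment and outcome measures: the secondary outcomes include "changes in the dosage of the prescribed drugs, as a reflection of changes in adherence to therapy".
- Ethical considerations gives the direction. Once response has improved, "as a result of greater adherence to pharmacotherapy, the therapist will decrease dosage of the prescribed drugs".
- Data management and analysis: the logistic model is for "controlling the impact of the confounding variables (sex, age, severity of the disorder, cluster", a list without dose.

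**The concern.** BARS ends in a percentage of doses taken, and the five MARS items used ask whether medication is taken. Neither moves when the prescription changes. A blood level does: at equal adherence, a patient prescribed twice the dose has roughly twice the level. With unrestricted prescribing, part of the variation in level reflects the prescriber and the drug rather than adherence. Dose reductions after improved adherence would pull the level down in the very patients whose scale scores rise.

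At stake is the validation of MARS and BARS, which the protocol offers to future studies, and the choice of scale for one of the two stated adherence indicators. Attenuation can make a valid scale look poor, and it narrows the gap between a better and a worse scale, so that chance decides more often.

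**Working it through.** The plan gives no figure for this comparison, so there is none to reproduce. The check asks how much an unmodelled dose could matter.

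**Inputs from the protocol.** 340 patients enrolled; 20% drop-out, so 340 × 0.80 = 272 analysed; non-adherence 47% in the unexposed and 25.5% in the exposed arm; 30% cut-off for non-adherence.

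**Assumptions (the protocol gives no values).** Level = dose × fraction taken × lognormal kinetic factor, log SD 0.3 or 0.5. Fraction taken is uniform on 0.2–0.7 for non-adherent and 0.7–1.0 for adherent patients. BARS is the fraction taken plus error of SD 0.10; MARS has error of SD 0.15 and is rounded to 0–5. Starting dose is unrelated to adherence. All patients take one drug, so differences between drugs are not modelled.

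**1. Dose spread alone, no cuts.** On the log scale, dose and kinetic variances add. If dose is lognormal, a coefficient of variation (CV) of 30% gives log variance ln(1 + 0.30²) = 0.086, and 50% gives ln(1 + 0.50²) = 0.223. With kinetic variance 0.3² = 0.09, the noise SD rises from 0.30 to √0.176 = 0.42 or √0.313 = 0.56. Simulated rho of BARS with level, 47% non-adherent, kinetic log SD 0.3:

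| Dose CV | Raw level | Level ÷ dose |
|---|---|---|
| 0 | 0.71 | 0.71 |
| 30% | 0.62 | 0.71 |
| 50% | 0.53 | 0.71 |

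A second model (fraction taken Beta(3, 1.5), scale error SD 0.15, dose log SD 0.4) gives the same pattern: 0.57 to 0.43 at kinetic SD 0.3, and 0.44 to 0.37 at 0.5. Its partial correlation given the other scale falls from 0.33 to 0.23 at kinetic SD 0.3.

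**2. Expected dose cuts, confined to net improvers.** Pooled non-adherence at the planned rates is (47 + 25.5)/2 = 36.25%, so 63.75% are adherent. Net improvers are (47 − 25.5)/2 = 10.75% of all patients, or 10.75/63.75 = 17% of the adherent. With equal starting doses and a 20–30% cut in that 17%:

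| Kinetic log SD | No cut | With cuts | Loss |
|---|---|---|---|
| 0.3 | 0.65 | 0.61–0.63 | 0.02–0.04 |
| 0.5 | 0.51 | 0.48–0.49 | 0.02–0.03 |

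**3. Widespread cuts (upper bound).** With 47% non-adherent and equal starting doses, a 20% cut in half of the adherent patients takes rho from 0.71 to 0.66, and a 30% cut in all of them takes it to 0.51 (kinetic SD 0.3). At kinetic SD 0.5 the fall is from 0.56 to 0.51 and 0.38.

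**4. Choosing the noisier scale.** The figures below are the share of runs in which MARS, noisier by assumption, shows the higher rho (dose CV 30–50%):

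| Cuts | Raw level | Level ÷ dose |
|---|---|---|
| None | 6–16% | 1–7% |
| 30% in half or all of the adherent | 11–26% | 1–9% |

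With cuts only in net improvers and equal starting doses, the two methods differ by only about one to two percentage points.

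**The case against.** The strongest reply is that the Medication section already commits to controlling dose, and that the bracketed covariate list is not exhaustive: family attendance and expressed emotion are declared confounders elsewhere and are missing from it too. How a level is expressed could also be left to the full protocol or the laboratory. This softens the point. A reader should not infer that the protocol ignores dose. But the Medication sentence follows one about balance between arms and names no analysis. The validation paragraph, by contrast, names its statistic, its variable and its conditioning variable, and dose is not among them.

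A second reply is right about size. A reader might infer from the protocol's own expectation that dose reductions cancel the signal. A patient who goes from 70% to 100% of doses with a 30% cut shows a level ratio of (1 − 0.30) × 1.00/0.70 = 1.00. That is a within-patient change, and no correlation of changes is stated. Nor does the protocol say which visits enter the correlation; at T0 no treatment-driven cut has yet occurred. Cuts are expected only after improvement, so the large losses in step 3 require cutting doses in patients who were adherent all along.

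The remedy also has limits. Dividing by dose assumes roughly linear kinetics, and ranking within drug may leave small strata.

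**Conclusion.** The point holds as a minor weakness of the validation analysis and of the choice of continuous index. As written, both use a blood level that mixes adherence with prescribed dose and drug. The main driver is between-patient dose spread: rho falls from 0.71 to 0.62 or 0.53 at an assumed dose CV of 30% or 50% with kinetic log SD 0.3. The expected dose reductions are secondary.

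The direction follows from the protocol's text, provided that dose does not itself rise with adherence. The sizes depend wholly on assumed dose spread, kinetic variation, scale errors and cuts.

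It would be wrong to read this as a threat to the trial's main comparison. The dichotomic index is built on self-report or interview, so neither it nor its between-arm test uses blood levels.

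**What to change.** In Data management and analysis, replace the raw blood level in both correlations with the level divided by the daily dose of that drug prescribed at the same assessment, ranked within drug. Where a drug has few patients or its kinetics are not close to linear, add prescribed dose and drug to the conditioning set of the partial correlation instead. Base the choice of continuous index on that comparison. Dosage change can stay as a secondary outcome.

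No new data are needed: Table 3 schedules the dosage record (DOTES) and the blood sample at T0, T1, T2 and T3, and Ethical considerations already has dosage changes checked at assessment. The cost is a sentence or two of text, the linearity assumption and some thin drug strata. The change would also carry out, for this analysis, what the Medication section promises.

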### Assessment tools

The MARS is a ten-item yes/no self-report instrument. Total scores vary from 0 (low likelihood of medication adherence) to 10 (high likelihood). From this scale, we used the five items specifically referring to the taking or not of the medication [31,32]. Therefore in our MARS version, total scores vary from 0 (low likelihood of medication adherence) to 5 (high likelihood).

The BARS is a brief, pencil-paper, clinician-administered adherence assessment instrument [33]. The BARS consists of four items: three questions and an overall visual analog rating scale to assess the percentage of doses taken by the patient in the past month (0% to 100%). The visual analog scale rating serves as a final adherence determination. The three questions inquire about patients’ knowledge of their own medication regimen and episodes of missed medication taking, and include: number of prescribed doses per day (question 1); number of days, over the past month, the patient did not take the prescribed doses (question 2); and number of days, over the past month, the patient took less than the prescribed doses (question 3). A higher score on the BARS corresponds to better adherence.

The CGI is a tripartite rating scale aimed at assessing the severity of the patient at the moment of the assessment, improvement or worsening relative to the baseline, and efficacy of treatment (described in [34]). The CGI-severity rating is provided on a seven-point scale that assesses severity of the patient on the basis of total clinical impression: 1) not at all ill; 2) borderline mentally ill; 3) mildly ill; 4) moderately ill; 5) markedly ill; 6) severely ill; or 7) extremely ill. The CGI-change is provided on a seven-point scale, rated as: 1) very much improved; 2) much improved; 3) minimally improved; 4) no change; 5) minimally worse; 6) much worse; or 7) very much worse. The CGI-efficacy index is a rating scale crossing the efficacy of the treatment by occurrence of side effects: 1) unchanged to worse; 2) minimal efficacy; 3) moderate efficacy; 4) marked efficacy, with side effects rated as: 1) none; 2) does not interfere with patient’s functioning; 3) interferes with patient’s functioning; 4) outweighs therapeutic effects. A higher score on the CGI-severity and the CGI-change rating corresponds to greater severity and worsening, respectively. Conversely, a higher score on the CGI-efficacy index corresponds to better efficacy (however, greater side effects counterbalance efficacy).

The BPRS is a 24-item measure of general psychopathology in a Likert format, with scores from 1 (absent) to 7 (extremely severe) [35,36]. Possible BPRS total scores varied from 24 to 168. The primary purpose of the BPRS is to allow assessment of treatment change across a comprehensive set of common symptom characteristics. The original 16-item BPRS was initially expanded to 18 items, then to 24 items by adding 6 symptom items (bizarre behavior, self-neglect, suicidality, elevated mood, distractibility, and motor hyperactivity) to increase sensitivity to a broader range of psychotic and affective symptoms [37]. A higher score on the BPRS corresponds to greater psychopathology.

The PANSS is a measure of the current symptoms of patients on a 30-item scale [38,39]. The PANSS consists of three domains: positive symptoms, negative symptoms, and general psychopathology. Items are rated from 1 (absent) to 7 (extremely severe); the total score varies from 30 to 210. A higher score on the PANSS corresponds to greater psychopathology.

The HoNOS comprises 12 items that rate various aspects of mental and social health with a severity score varying from 0 (no problem) to 4 (severe to very severe problem). These items are grouped in four subscales: behavioral problems, impairment problems, symptoms problems and social problems [40]. Clinicians rate HoNOS before and after interventions, so that changes attributable to the interventions (outcomes) can be measured [41]. A higher score on each HoNOS subscale corresponds to greater occurrence of problems in the corresponding areas.

The PSP is a version of the Global Assessment of Functioning [42], with detailed instructions on how to rate the functioning of the patient [43]. The PSP rates the social and occupational functions of patients; its scores vary from 1 to 100, with a score of 100 indicating excellent functioning.

The WHOQOL-Bref is a relatively new instrument, used to measure quality of life. It is an abbreviated version of the WHOQOL-100 quality of life instrument, developed by the WHOQOL group [44,45]. The WHOQOL-Bref adopts the following definition of health-related quality of life: ‘the value assigned to duration of life as modified by the impairments, functional states, perceptions, and social opportunities that are influenced by disease, injury, treatment, or policy’ [46]. It produces scores for four domains related to the quality of life (physical health, psychological sphere, social relationships and the environment). The Italian version used in this study was also reported to have satisfactory psychometric properties [47]. The items are rated on a five-point Likert scale, reflecting intensity, capacity, frequency or evaluation. The items inquire ‘how much’, ‘how completely’, ‘how often’, ‘how good’ or ‘how satisfied’, with possible answers varying from ‘very satisfied’ to ‘not at all satisfied’. The scores in each domain vary from 4 to 20, where a higher score indicates a better quality of life.

### Expressed emotion in the patient’s family

The concept of expressed emotion (EE) was developed to describe the emotional environment and the attitude of caregivers towards a relative affected by a disorder. The Camberwell Family Interview (CFI) is the standard reference for this type of study [48], and measures the amount of critical comments (CCs), hostility (H), or emotional over-involvement (EOI) expressed by a close relative when talking about a mentally or physically ill family member. High EE consistently predicts the risk of relapse for patients with schizophrenia [49,50], but the CFI is time-consuming, and requires detailed training of the assessors. The Family Questionnaire (FQ) is a brief self-report questionnaire aimed at measuring expressed emotion on a four-point Likert scale, from 0 (never/rarely) to 4 (often/always) [51]. The FQ provides two subscale scores: critical comments (CC) and emotional over-involvement (EOI). Scores of 24 or higher on the CC subscale or 28 or higher on the EOI subscale define the occurrence of EE in the family. The FQ was proved to relate to EE rating by the CFI. FQ scores will be analyzed both as a confounding variable to explore the role of EE in the effectiveness of psychoeducation, and as an outcome measure to evaluate whether FPP or GT can improve EE levels in the patient’s family.

